# Effects of video-guided active breaks with curricular content on mental health and classroom climate in chilean schoolchildren aged 6 to 10: study protocol for a multicentre randomized controlled trial

**DOI:** 10.3389/fphys.2024.1438555

**Published:** 2024-09-12

**Keywords:** physical exercise, school climate children, physical fitness, primary school, school-based intervention, RCT

## Abstract

**Background:**

The incidence of mental health issues in children is increasing worldwide. In Chile, a recent surge in reports of deteriorating mental health among school populations and an increase in complaints related to poor school climate have been observed. Physical activity, specifically active breaks in the classroom, has shown positive effects on children’s health. However, evidence regarding its impact on mental health and school climate in children is limited.

**Objective:**

This work outlines the design, measurements, intervention program, and potential efficacy of the “Active Classes + School Climate and Mental Health” project. This project will assess a 12-week program of active breaks through guided videos with curricular content in the school classroom, and its effects on mental health and school climate as its primary indicators. Additionally, it will measure physical activity, physical fitness, motor competence, and academic performance in students aged 6–10 years in the Biobío province, Chile, as secondary indicators. Methodology: A multicenter randomized controlled trial involving 823 students from 1st to 4th grade (6–10 years old), six schools (three intervention and three control) will be conducted in the Biobío region, Chile. Participants belonging to the intervention group will implement video-guided active breaks through the “Active Classes” web platform, featuring curricular content, lasting 5–10 min and of moderate to vigorous intensity physical activity, twice a day, Monday to Friday, over a span of 12 weeks. Expected Results/Discussion: To our knowledge, this will be the first study in Chile to evaluate the effects of incorporating video-guided active breaks with curricular content on mental health variables and school climate in schoolchildren. Thus, this study contributes to the scarce evidence on the effects of video-guided active breaks on mental health variables and school climate in schoolchildren worldwide. Additionally, it will provide crucial information about active teaching methodologies that have the potential to positively contribute to the wellbeing of students, thus addressing the problems of mental health and climate in Chilean schools. ClinicalTrials.gov ID NCT06423404.

## Introduction

Mental health is a complex state that goes beyond the absence of illness, encompassing emotional wellbeing, functionality, adaptability, and cultural and contextual factors. This construct has been approached from multiple perspectives. Cyranka (2020) defines mental health as a dynamic state of internal equilibrium that allows individuals to use their abilities in harmony with the universal values of society. In that line, the World Health Organization (WHO) describes it as a state of wellbeing in which the individual realizes their own abilities, copes with the normal stresses of life, works productively, and contributes to their community. Finally, Huber et al. (2011) highlight adaptability and self-management as key elements of mental health.

The previous definitions recognize two major groups of underlying determinants: biomedical, and sociocultural. The former refers to emotional and spiritual wellbeing, internal balance, cognitive and social skills, and the capacity for adaptability and self-management (Cyranka, 2020); while the latter refers to the ability to interact effectively with the environment and other people, and to the importance of culture, social justice, equity, and personal dignity (Wren-Lewis and Alexandrova, 2021). Additionally, behavioral and lifestyle factors, such as physical activity, fitness (Andermo et al., 2020; Poitras et al., 2016; Rodriguez-Ayllon et al., 2019), sleep quality (Scott et al., 2021), and diet (Głąbska et al., 2020), are associated with mental health.

The recent global prevalence of mental health disorders in children aged 5–9 years was reported to be 15.5%, increasing to 28% among those aged 10–14 years (World Health Organization, 2022). The COVID-19 pandemic is a factor that has worsened the mental health of this age group, surpassing its impact on the adult population (Organization for Economic Co-operation and Development OECD, 2021). This has resulted in heightened symptoms of anxiety, depression, fear, anger, and irritability (Panchal et al., 2023; Samji et al., 2022; United Nations Children’s Fund UNICEF, 2021).

In this regard, various studies indicate a further deterioration of the mental health of the school population in Chile due to the pandemic (Larraguibel et al., 2021; Sáez-Delgado et al., 2020; Santa-Cruz et al., 2022). Prior to the pandemic, Chile had already ranked among the countries with the highest prevalence of mental health disorders, particularly in the population aged 4–11 years (Ministerio de Salud, 2017; Vicente et al., 2016).

On the other hand, there is the concept of school climate, which has been defined as a construct encompassing various dimensions within the educational community. Generally, it refers to the relationships within the school, the support for students, and the perceptions of both students and staff about the overall school environment. Factors influencing school climate include interpersonal relationships, safety, social and emotional support, academic structure, and the institutional environment (Kupchik et al., 2022). When considering school climate, physical activity can enhance social cohesion and a sense of belonging among students, contributing to a more positive school environment (Langford et al., 2015). The self-determination theory (Deci and Ryan, 1985) provides a useful framework for understanding how physical activity can influence school climate. By satisfying the basic psychological needs of autonomy, competence, and relatedness, physical activity not only improves the mental health and wellbeing of students but also contributes to a more positive and cohesive school environment.

In line with the above, Benítez-Sillero et al. (2021) present evidence showing that physical activity has a positive influence on the school climate. First, the satisfaction of basic psychological needs, described by the Self-Determination Theory (SDT) as autonomy, social competence, and relatedness (Lavigne et al., 2016), allows students who participate in physical activities to feel more competent and connected with their peers, which can lead to a better school climate by promoting positive interactions and a sense of belonging. Additionally, the reduction of stress and improvement in psychological wellbeing foster a positive climate, with fewer conflicts and greater collaboration between students and teachers (Benítez-Sillero et al., 2021; Fernández-Bustos et al., 2019; Mücke et al., 2020). Finally, in terms of bullying prevention, well-structured and regular physical activity programs can act as a protective factor against bullying victimization (Hormazábal-Aguayo et al., 2019; Zych et al., 2019).

In response to the high levels of poor school climate indicators and mental health issues within the educational context, and in alignment with international guidelines (World Health Organization, 2013), Chile has implemented a National School Climate Policy. This policy aims to guide and strengthen the teaching, learning, school climate, and overall student development (Ministerio de Educación, 2019). Additionally, it was supported by the National Mental Health Plan for 2017–2025 (Ministerio de Educación, 2020). Both public policy initiatives emphasize the need to comprehensively address the issues of school climate and child mental health, reinforcing promotion and prevention actions aims to guide and strengthen the teaching, learning, school climate, and overall student development (Ministerio de Educación, 2019; Ministerio de Salud, 2021).

Mental health and school climate can theoretically be linked through (Bronfenbrenner, 1979), which considers multiple systems of influence on the individual, from the immediate environment to broader policies. For example, a positive climate in the microsystem (i.e., the school) can provide a supportive, secure, and adaptive environment for students. Empirically, studies have shown that a positive school climate is associated with lower levels of anxiety and depression among students (Espelage et al., 2014; Holfeld and Baitz, 2020). Additionally, some studies suggest a positive impact of the pandemic, with a reduction in cyberbullying and improved school climate (Bacher-Hicks et al., 2022). In Chile, there has been an increase in reports related to school climate in 2022 compared to 2018 and 2019, indicating a rise in violence among students, reports of mistreatment of teachers, and instances of discrimination (Ministerio de Educación and Centro de Estudios, 2023). This highlights the importance of promoting physical activity programs in schools as a comprehensive strategy to improve both the mental health of students and the school climate.

In this context, regular physical activity has been associated with better mental health (Biddle and Asare, 2011; Penedo and Dahn, 2005), including the reduction of symptoms of depression and anxiety (Morgan et al., 2013), as well as improvements in cognitive function and social relationships (Eime et al., 2013). An increase in wellbeing and resilience has also been observed. Although studies consistently show that men participate in physical activity more than women, with this pattern beginning in adolescence and continuing into adulthood, the mental health benefits of physical activity are similar between genders (Biddle and Asare, 2011; Eime et al., 2013).

Physical activity and exercise are recognized as protective factors in the prevention and treatment of various health conditions and are associated with better mental health (Biddle and Asare, 2011; Eime et al., 2013; Hillman and Biggan, 2017; World Health Organization, 2020). High levels of physical activity and fitness in children have been linked to better mental health (Andermo et al., 2020; Poitras et al., 2016; Rodriguez-Ayllon et al., 2019). Additionally, there is recent evidence indicating that a high level of physical activity in childhood develops motor skills related to the level of physical activity in adulthood (Engel et al., 2018). The Global Action Plan on Physical Activity 2018–2030 suggests an inclusive approach in the school environment that promotes the participation and integration of physical activity in various educational contexts (World Health Organization, 2018). Therefore, active commutes, recesses, physical education classes, and especially the classroom, make the school an ideal environment for promoting physical activity and mental health (Langford et al., 2015; Ministerio de Salud, 2017; O’Connor et al., 2018).

Specifically, physical activity interventions in the classroom have a growing body of evidence supporting their positive effects (McDonald et al., 2018), including increased physical activity levels (Masini et al., 2020), academic performance (Bedard et al., 2019; Watson et al., 2017a), cognitive functions (Daly-Smith et al., 2018; Donnelly et al., 2016), attention, and classroom behaviour (Carlson et al., 2018). More recently, two reviews have reported the positive effects of such interventions on indicators associated with the wellbeing and mental health of the school-age population (Papadopoulos et al., 2022; Robles-Campos et al., 2023).

One type of physical activity intervention in the classroom is active breaks, characterized by brief periods of physical activity as breaks from regular academic activities with or without curricular content (Robles-Campos et al., 2023; Sánchez-López et al., 2020; Watson et al., 2017a). Active breaks, particularly when guided by video, have evidence supporting their effectiveness in addressing common barriers identified in implementing physical activity in the school setting, including the low competence and self-perception of classroom teachers in guiding physical activity. These barriers reported by teachers are mainly addressed because, being a tool that only requires having a computer and clicking, it becomes more feasible. It does not involve extensive planning or time usage as required for conventional interventions (Nathan et al., 2018; Vaquero-Solís et al., 2020).

A recent scoping review by Robles-Campos et al. (2023) on active breaks reported their positive effects on the mental health of the school-age population, indicating that the most effective active breaks for mental health variables in 6–12-year-olds are video-guided breaks that include curricular content. These breaks are conducted 2 to 5 times per week, lasting 4–10 min, and involve aerobic exercise, muscular strength, and/or motor games (Robles-Campos et al., 2023). However, despite initiatives incorporating video-guided active breaks in the classroom through interactive platforms, with evidence of positive effects on health variables, such as brain breaks (Glapa et al., 2018; Koch et al., 2019; Mok et al., 2020) and EUmove (Sánchez-Oliva et al., 2022), and in Chile with initiatives such as ACTIVA-MENTE (Ministerio de Educación, 2020), there is a lack of studies examining the effects of these video-guided active breaks on school climate.

Specifically, in Chile, the impact of such interventions on variables such as mental health, physical activity, physical fitness, motor competence, and academic performance in school-age populations remains unknown. In particular, the potential effect of this type of classroom intervention on mental health and climate problems in Chilean schools is unknown. It is of clinical and public health relevance to understand whether active teaching methodologies, such as video-guided school active breaks in the classroom, can improve the wellbeing of Chilean schoolchildren and thus address the problems of mental health and climate in Chilean schools. Therefore, due to the lack of studies examining the effects of video-guided active breaks on mental health and school climate, this study aims to describe the methods and rationale of an active breaks intervention (“Active Classes + School Climate and Mental Health”) to improve mental health and school climate (primary outcome), physical activity, physical fitness, motor competence, and academic performance (secondary outcomes) in 6 to 10-year-old schoolchildren in the Biobío region of Chile.

## Methodology

### Study design

This study adopts a multicenter, cluster, randomized, double-blind (evaluator and data analyst blind to each other) controlled trial design, with two arms, registered on ClinicalTrials.gov under the identifier NCT06423404, as of 20 March 2024. Six public educational centers in the Biobío region, Chile, were invited to participate (two from Biobío province, two from Arauco province, and two from Concepción province). The study followed the CONSORT guidelines for clinical trials (Butcher et al., 2022), reporting on social and psychological interventions (Montgomery et al., 2018), and the SPIRIT guidelines for protocol studies (Chan et al., 2013).

### Study setting

This project targets public primary schools within the Biobío province, Chile, that share similar School Vulnerability Index (SVI) levels and fall within the medium to low socioeconomic bracket. The chosen schools are characterized by a daily schedule that spans roughly 8 hours (8:00 a.m. to 4:00 p.m.), segmented by two 15-min breaks (9:45 A, to 10:00 and 11:30 to 11:45 generally) and an extended 1-h lunch break (13:30 to 14:30). The study’s intervention specifically targets students in 1st to 4th grade. As can be seen in Figure 1, for the purposes of this research, six schools will be selected: half will participate in the intervention arm, while the other three will serve as the control group. This will result in a total sample size of approximately 820 students, assuming an average of eight classes per school, with each class comprising 30 to 40 students. All classes will continue with their physical education lessons, which correspond to 3 pedagogical hours per week according to the participating educational levels (See Figure 1).

**FIGURE 1 F1:**
[figure not shown]
Flowchart of the active classes study. Note. C.E. = Educational Centre.

### School recruitment

To engage educational centers, recruitment will begin with an initial outreach through email, followed by phone calls to extend a formal invitation. This process is informed by consulting the MINEDUC database (accessible at https://datosabiertos.mineduc.cl). A researcher from our project team has already held discussions with the regional Ministerial Secretary of Education for the Biobío region and directors of provincial education. Further, meetings are planned with the management teams of schools showing interest. Schools that agree to participate will be provided with a concise project overview, written in accessible language, alongside an authorization form. This form needs to be signed and returned to confirm their participation.

#### Criteria for school selection

The selection process for schools participating in the experimental evaluation will be guided by specific criteria: urbanity, administrative structure, student enrollment size, and academic performance. Drawing on data from the educational system, we identify eligible schools within the Biobío region, which has 1022 urban schools. Rural schools will be excluded due to limitations such as smaller sample sizes and the presence of multi-grade classrooms. The focus will be solely on public schools, categorized into municipal, delegated administration, and Public Local Services (PELS), totaling 372 potential schools in the region. After eliminating schools offering only secondary education, the selection narrows to 192 schools. Additionally, single-gender schools—two in Arauco and two in Concepción—are excluded.

A crucial criterion is the enrollment size, specifically targeting medium-sized schools with 300–500 primary students, ensuring a minimum of two classes per grade level from 1st to 4th grade. This range guarantees sufficient sample size while excluding schools under 300 for lack of two classes per grade and those over 500 to avoid the complexities of larger school dynamics, hypothesized to have a higher likelihood of school climate conflicts. Consequently, the selection is reduced to 41 schools.

The academic trajectory, as classified by the Agency for Quality in Education (ACE)—insufficient, low-medium, medium, and high—further narrows the field. This study will focus on schools classified as ‘medium,’ anticipated to perform according to academic and personal/social development expectations relative to their socio-demographic context. This choice is made considering that low-performing schools while challenging for implementation, may exhibit rapid gains, whereas high-performing schools might show slower progress. With these criteria, the pool of eligible schools reduces to 23: 5 in Arauco, 6 in Biobío, and 12 in Concepción.

For final selection, six schools (two schools per province) will be chosen based on the enthusiasm and commitment of the educational leadership, staff, and teachers, as well as the school’s connectivity and resources.

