## Randomization of participating schools

After securing participation from schools, they will be randomly allocated to one of two groups through a sequence generated by the IBM SPSS software, ensuring concealed allocation. The groups are: 1) the Experimental Group (n = 3; 1 for each province), which will partake in a 12-week program of video-guided active breaks incorporating curricular content within the school classroom setting; and 2) the Control Group (n = 3; 1 for each province), which will receive the intervention after the conclusion of the initial data collection phase. This randomization allowed each province to have an experimental group and a control group. The random sequence will be kept confidential using sequentially numbered, opaque, sealed envelopes, managed by a researcher who will not interact with the schools or participants. Previous research with similar participant samples has identified significant differences in quality of life, motor skills, and academic performance, underscoring the potential impact of our intervention (Sánchez-López et al., 2019; Watson et al., 2017a).

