Mixed model analyses will be carried out to establish differences in school climate and mental health between the experimental group (video-guided active breaks incorporating curricular content within the school classroom setting) and the control group. The fixed effects of the model are group (Experimental versus control), times (Pretest; Posttest), and their interaction over time (Time x Group). The schools in the models will have a random effect to capture the hierarchical structure of the data and handle the possible dependence of observations within each school. To compare the probability of a model with the effect included versus a model with the effect excluded, the likelihood ratio test (LRT) will be used for the random effect. Additionally, the intraclass correlation coefficient (ICC) will be estimated to quantify the proportion of the total variance attributed to the variance between clusters (schools). Post-hoc tests will be performed using Holm’s correction for multiple comparisons. For all analyses, a significance level of *p* < 0.05 was established. Models will adjust for multiple covariates, such as demographic characteristics (e.g., age, gender) and secondary study variables, that could influence school climate and mental health outcomes. All analyses will be performed using Jamovi statistical software version 2.0.0.0 (The Jamovi Project).

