To the best of our knowledge, this is the first study in Chile to investigate the effectiveness of a guided active break intervention with curricular content in the school classroom and its effect on mental health and school climate (primary outcome), physical condition, and academic performance (secondary outcomes) in students aged 6–10 years in the Biobío province, Chile. This study and its possible findings are of utmost relevance in addressing mental health problems and school climate in Chilean schools. In this way, it will contribute significantly to knowledge by reporting the results of this type of intervention on mental health variables and the school climate. In addition, it will include the development and implementation of an interactive web platform for active breaks along with a protocol for the application of these video-guided active breaks in the school classroom. This information will be very useful if other educational establishments show interest in its implementation or even if you wish to implement a national strategy based on video-guided active breaks. Additionally, this study presents methodological characteristics that make it novel. Very few studies have evaluated the effect of active breaks across a wide range of variables and in such a large sample. This is the first study to focus on the effects of active breaks on school climate and mental health as primary outcomes. This point is relevant as it proposes a novel alternative in the school context to address current challenges in school climate, particularly in the early years of education.

However, our protocol has some limitations. Specifically, the effects of the intervention are assessed using only two groups: one experimental and one control. This makes it challenging to determine whether the observed findings are attributed to the nature of active rest involving physical activity, or simply due to the interruption of academic activity. Therefore, we recommend creating “placebo groups” for future research to compare the impact of active breaks with academic content, sedentary breaks with academic content, and the control group.

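### School enrolment cannot guarantee a sufficient sample when six schools are randomised: the stated sufficiency is unsupported, and the primary outcomes need intervals on school-level degrees of freedom

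*Protocol article*

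**What the plan says.** Under Criteria for school selection, the article explains its enrolment limit as "specifically targeting medium-sized schools with 300–500 primary students, ensuring a minimum of two classes per grade level from 1st to 4th grade", and then adds: "This range guarantees sufficient sample size while excluding schools under 300 for lack of two classes per grade". Study setting counts the sample in pupils: "This will result in a total sample size of approximately 820 students". Under Randomization of participating schools, the unit is the school, with three per arm: "This randomization allowed each province to have an experimental group and a control group". That section also appeals to earlier work: "Previous research with similar participant samples has identified significant differences in quality of life, motor skills, and academic performance". It gives no effect size or variance from that work.

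Statistical analysis plans a mixed model with group, time and Time x Group as fixed effects. It puts a random effect on school to "handle the possible dependence of observations within each school", and the ICC will be estimated from the trial data. The same section also describes a two-way repeated-measures ANOVA with the same effects and no school term.

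**The concern.** In a cluster trial the information on the treatment effect comes from two sources: the number of clusters and the number of pupils within them. An enrolment range controls only the second. Once schools differ, or change differently over 12 weeks, precision is limited by having three schools per arm, however many pupils each one supplies. The article expects such dependence in its own analysis section, yet offers school size as a guarantee.

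Two things are at stake. A reader may take the pupil count as the measure of what the trial can detect, which is far too favourable for most plausible ICCs. And if the analysis does not carry the small number of schools into the standard error of Time x Group, the intervals and p-values will not reflect it either.

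**Working it through.** **The article's own figure.** Study setting derives the total from 6 schools, 8 classes per school and 30 to 40 pupils per class: 6 x 8 x 30 = 1,440 and 6 x 8 x 40 = 1,920. About 820 would be 43% to 57% of that (820/1,920 and 820/1,440). Only pupils with parental consent supply data, so the gap may reflect consent, but no rate is given. I take the stated total at face value: 820/6 = 137 pupils per school.

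**Inputs.** From the article: 3 v 3 schools and a significance level of 0.05. Assumed, because the article gives none: two-sided test, 80% power, ICC 0.01 to 0.10, equal school sizes, no dropout, and 4 df (6 schools minus 2).

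**Pupil-count benchmark.** With 820 independent pupils the detectable difference would be 2.80 x sqrt(4/820) = 0.20 SD.

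**Post-test comparison.** With m pupils per school and the outcome in SD units:

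Var = (2/3) x [ICC + (1 - ICC)/m]

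The ICC term does not contain m. The detectable difference is 3.76 x sqrt(Var), where 3.76 is the noncentrality that gives 80% power for t on 4 df. Example, ICC 0.05 and m = 137: (2/3) x (0.05 + 0.95/137) = 0.0380; square root 0.195; x 3.76 = 0.73.

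**Using baseline.** Multiply Var by (1 - r²), where r is the pre/post correlation of school means. If the correlation is 0.6 at both school and pupil level, the factor on the SD scale is sqrt(1 - 0.36) = 0.8. If school effects correlate 0.8 over time and pupils 0.6, r = [0.8 ICC + 0.6(1 - ICC)/m] / [ICC + (1 - ICC)/m], which is 0.72 to 0.79 for m = 137.

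**Time x Group as a difference in change.** With ρs the school correlation and ρi the pupil correlation over time:

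Var = (4/3) x [ICC(1 - ρs) + (1 - ICC)(1 - ρi)/m]

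The first term again does not contain m. It vanishes only if school effects are perfectly stable (ρs = 1).

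Detectable difference (SD):

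| Setting | ICC 0.01 | 0.02 | 0.05 | 0.10 |
|---|---|---|---|---|
| 137 per school, no baseline | 0.40 | 0.51 | 0.73 | 1.00 |
| Unlimited pupils, no baseline | 0.31 | 0.43 | 0.69 | 0.97 |
| 68 per school (outcomes in two grades only), no baseline | 0.48 | 0.57 | 0.78 | 1.03 |
| 137, baseline, 0.6 at both levels | 0.32 | 0.40 | 0.59 | 0.80 |
| 137, baseline, school 0.8 and pupil 0.6 | 0.28 | 0.34 | 0.46 | 0.62 |
| Unlimited, baseline, school 0.8 | 0.18 | 0.26 | 0.41 | 0.58 |
| 137, difference in change, 0.6 and 0.6 | 0.36 | 0.45 | 0.66 | 0.90 |
| 137, difference in change, 0.8 and 0.6 | 0.30 | 0.36 | 0.49 | 0.65 |

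The baseline rows keep 4 df. Estimating a school-level baseline slope would cost one more and raise the 0.28 to 0.62 row to 0.32 to 0.70.

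**Power, 137 per school, no baseline.** For d = 0.5: 93% at ICC 0.01 and 50% at ICC 0.05. For d = 0.3 at ICC 0.05: 22%. With baseline (0.8 and 0.6) at ICC 0.05, power for d = 0.5 is 85%.

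**What the stated mixed model does with this.** Read the random effect on school as an intercept. It absorbs stable school differences, so Time x Group is judged against pupil-level residuals, with variance about (4/3) x [(1 - ICC) + ICC(1 - ρs)]/m. For ICC 0.05, m = 137 and both correlations 0.6:
- model variance: (4/3) x 0.97/137 = 0.0094
- actual variance: (4/3) x (0.05 x 0.4 + 0.95 x 0.4/137) = 0.0304
- type I error: about 2 x [1 - Φ(1.96 x sqrt(0.0094/0.0304))] = 27%

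With ρs = 1 the actual variance is (4/3) x 0.95 x 0.4/137 = 0.0037, and the same formula gives about 0.2%, which is conservative. A simulation over assumed ICC 0.02 to 0.10 with pupil correlation 0.6 agrees: type I error ran from under 1% to about 50% for this model, and stayed near 5% for a school-level analysis on 4 df.

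**The case against.** Several counter-arguments have force.

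- **The sentence may concern recruitment, not power.** It stands among school selection criteria next to the class-count reason, and it names no effect or precision. That reading is possible. But the sentence gives the class count as its own reason beside the size claim. If only pupils and classes per school were meant, removing the guarantee loses nothing.
- **A reader might infer that the sample has been shown to be too small.** The article does not support that. It gives neither ICC nor target effect, and at ICC 0.01 power for d = 0.5 is 93% even without baseline.
- **The unadjusted figures are not those of the planned analysis.** This is correct. The plan compares change between groups, so stable school differences cancel. The baseline and change rows are the relevant ones, and they are clearly lower. They still carry a school-level term that enrolment does not touch.
- **A reader might infer that a non-significant result would be reported as no effect.** No passage says so. The Discussion's phrase "across a wide range of variables and in such a large sample" compares the trial with earlier active-break studies; it is a remark on novelty, not a claim about power.
- **A journal article may leave the power calculation to the full protocol.** It may, and its absence is not the point. The point is a guarantee that the design cannot give, and a random effect, as described, that does not supply the right error term for Time x Group.

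**Conclusion.** The concern holds in limited form. That enrolment cannot guarantee a sufficient sample with three schools per arm follows from the design whenever schools differ in their change over time, and it needs no outside figure. Whether the sample is in fact sufficient cannot be settled from the article.

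For scale, with 137 pupils per school, 80% power and 4 df, the detectable difference over ICC 0.01 to 0.10 is 0.40 to 1.00 SD unadjusted, 0.32 to 0.80 SD with baseline correlation 0.6, and 0.28 to 0.62 SD with more stable school means. The pupil count would suggest 0.20 SD. The ICCs and correlations are assumptions. On the article's own bands, the planned type of analysis could reach part of the small range (0.2 to 0.49) if the ICC is low, and only moderate or larger effects if it is near 0.10.

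The more consequential part is the error term. As described, the mixed model can make the Time x Group test much too liberal or too conservative, depending on how stable school means are. This rests on reading the random effect as a school intercept only, since no school-by-time or pupil effect is mentioned.

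**What to change.** 1. **Criteria for school selection:** keep the reason of at least two classes per grade and delete the guarantee of sample size.
2. **Study setting:** describe the size as six schools, three per arm, with the expected pupils per school. Give the detectable difference for the planned baseline-using analysis over a stated ICC range, with the assumed stability of school means.
3. **Statistical analysis:** report each primary outcome as an estimate with a 95% interval on school-level degrees of freedom. Either an analysis of school mean changes or a mixed model with a school-by-time random effect and a small-sample df correction would do this.

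The cost is a few sentences, one short calculation and a change of model specification, with no added schools or pupils. The downside is intervals that will often be wider, and a less favourable statement of what the trial can detect.
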